## Abstract

**Introduction:**

The COVID-19 pandemic has had profound effects on the working lives of healthcare workers (HCWs), but the extent to which their well-being and mental health have been affected remains unclear. This longitudinal cohort study aims to recruit a cohort of National Health Service (NHS) HCWs, conducting surveys at regular intervals to provide evidence about the prevalence of symptoms of mental disorders, and investigate associated factors such as occupational contexts and support interventions available.

**Methods and analysis:**

All staff, students and volunteers working in the 18 participating NHS Trusts in England will be sent emails inviting them to complete a survey at baseline, with email invitations for the follow-up surveys sent 6 months and 12 months later. Opening in late April 2020, the baseline survey collects data on demographics, occupational/organisational factors, experiences of COVID-19, validated measures of symptoms of poor mental health (eg, depression, anxiety, post-traumatic stress disorder), and constructs such as resilience and moral injury. These surveys will be complemented by in-depth psychiatric interviews with a sample of HCWs. Qualitative interviews will also be conducted, to gain deeper understanding of the support programmes used or desired by staff, and facilitators and barriers to accessing such programmes.

**Ethics and dissemination:**

Ethical approval for the study was granted by the Health Research Authority (reference: 20/HRA/210, IRAS: 282686) and local Trust Research and Development approval. Cohort data are collected via Qualtrics online survey software, pseudonymised and held on secure university servers. Participants are aware that they can withdraw from the study at any time, and there is signposting to support services if participants feel they need it. Only those consenting to be contacted about further research will be invited to participate in further components. Findings will be rapidly shared with NHS Trusts, and via academic publications in due course.

Strengths and limitations of this studyThe longitudinal cohort design addresses the lack of long-term data on this population, and the current predominance of cross-sectional evidence available.The availability of Trust Human Resources data means we will be able to calculate response rates, and weight the data appropriately.The diagnostic interview component of the study will allow us to establish the true prevalence of mental disorders, which can be inflated by the measures used in most mental health and well-being cohort studies.The qualitative interviews will give deeper insight into the support programmes that healthcare workers (HCWs) find most helpful, and provide ideas for Trusts to improve their offer to staff.The three components of the study give breadth and depth lacking in much of the mental health and well-being research currently available, but there is a risk of overburdening already stretched HCWs.

## Introduction

The COVID-19 pandemic raises many questions on biological, behavioural, emotional and social responses to a global threat.^1^ Evidence from systematic reviews and meta-analyses suggests that healthcare workers (HCWs) who have had to deal with serious infection during pandemics in the past (severe acute respiratory syndrome (SARS), Middle East respiratory syndrome (MERS), Ebola, swine influenza) are at increased risk of both current and subsequent mental health problems.^2 3^

Pandemics expose HCWs to overwork, isolation from friends and family, discrimination, exhaustion and an increased risk of developing common mental disorders.^3^ Early accounts from Wuhan, China, confirm this, suggesting that the added pressures of providing healthcare during a pandemic can result in impaired decision making, attention and understanding thereby hindering the control of the pandemic, but also early signs of distress may well lead to longer-term mental ill-health.^4^ A relatively new concept that has attracted a lot of attention is the concept of ‘moral injury’.^5^ Moral injury describes the psychological distress resulting from actions, or the lack of them, which violate someone’s moral or ethical code and can contribute to the development of mental health difficulties, including depression, post-traumatic stress disorder (PTSD) and suicidal ideation.^6^ During the COVID-19 pandemic many National Health Service (NHS) staff may have had to make difficult choices not faced before, to deliver care that they know is suboptimal and to explain difficult decisions to relatives. Such ethical dilemmas will be new in scale and nature.

Research to date suggests that women, younger people, and those from racial and ethnic minority groups are at higher risk of adverse outcomes.^7^ There is evidence that those in lower income brackets have been more negatively affected,^8^ and that nurses may be worse affected than those in other roles.^9^ In terms of trajectory, well-being appears to have worsened during the early stages of the pandemic, with small improvements through the following months.^8^ Other factors associated with poor mental health and well-being are lack of access to personal protective equipment (PPE) and lack of supportive environments.^10^ While research on moral injury has previously focused on military contexts, early work in healthcare settings shows concerning associations with poorer outcomes.^10 11^

Much of the existing research in this area is based on single questionnaire assessments, typically only including clinical staff rather than all HCWs, from which bold claims of mental health crisis are made. While survey data can be informative, two-stage epidemiological studies using diagnostic interviews tend to show that such surveys overestimate prevalence of mental disorders.^12^ To address these issues, our study has five distinct features: (1) Breadth geographically, with a range of different types of NHS Trusts (eg, acute, mental health) and locations (urban, rural, all areas of England); (2) Depth phenotypically, with diagnostic interviews included in order to ascertain true prevalence of mental disorders rather than simply indicators of distress; (3) Longitudinal data collection to look at temporal patterns, meaning we will be able to identify whether a surge of symptoms at time of crisis lead to persistence or remission; (4) Inclusivity regardless of role, meaning that we will include all HCWs who are contributing to the pandemic effort, whether they are in clinical or ancillary and support roles; and (5) The ability to calculate accurate response rates and weight data appropriately, thanks to demographic population data provided by each participating Trust’s Human Resources department.

## Aims, objectives and hypotheses

The main aim of the study is to investigate the psychosocial impacts of the COVID-19 pandemic on NHS Trust workforce mental health and well-being over time. In addition, we aim to explore the uptake and usefulness of staff support interventions available to participants.

The primary objective is to establish a cohort of all staff employed in participating NHS Trusts, to carry out repeated surveys of their mental health and well-being and psychiatric diagnostic interviews to determine the true prevalence of disorders. Based on the literature outlined above, we have a number of descriptive aims and hypotheses. We will:

Describe the prevalence of psychological distress and characteristics associated with poorer mental health. Hypotheses include:*Poorer mental health will be associated with demographic variables (including younger age, female sex, coming from Black, Asian, or other racial or ethnic minority groups*).*Poorer mental health will be associated with occupational characteristics (including role, pay grade, work setting, redeployment status*).Establish the true prevalence of mental disorders via diagnostic interviews.Secondary objectives include exploring the factors associated with poor mental health, patterns of reported distress over time, and qualitatively exploring experiences of staff support interventions. We will:Describe workplace factors associated with poorer mental health. Hypotheses include:*Poorer mental health will be associated with higher levels of reported moral injury*.*Poorer mental health will be associated with reported lack of access to PPE*.*Poorer mental health will be associated with perceived lack of support from leaders, team, friends/family*.Describe patterns and persistence of psychological distress symptoms over time. Hypotheses include:*Mental health and well-being will follow the trajectory of the pandemic, with poorer outcomes evident during/after higher levels of COVID-19 prevalence (eg, as measured by daily deaths, hospital admissions*).*Poorer mental health at baseline will be associated with poorer mental health at 6-month and 12-month follow-up points*.*Predictors of poorer mental health at follow-up time points will include younger age, female sex, racial or ethnic minority group, being a nurse, perceived lack of support, lack of access to PPE, and higher levels of reported moral injury*.Qualitatively evaluate tiered and tailored staff support programmes being implemented locally and nationally, using in-depth interviews and thematic analysis. This will enhance our understanding of how we could further scale up effective support programmes within and across Trusts.Provide a platform for further randomised controlled trials (RCTs), and observational or intervention studies, including:An ethnic inequalities module, which will explore ethnic inequalities in mental health and occupational outcomes across NHS staff and the mechanisms that perpetuate these inequalities, using a mixture of quantitative and qualitative data (Tackling Inequalities and Discrimination Experiences in health Services Study: TIDES https://tidesstudy.com).Estimation of parameters of interest which could be later incorporated when designing an RCT or a pragmatic trial, for example, prevalence of psychosocial distress, intraclass correlation coefficient across the NHS Trust.An RCT testing a well-being app for use by NHS staff.

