
## Methods

### Design and setting

This study consists of three main components:

A longitudinal cohort study, consisting of surveys administered at baseline, 6 months and 12 months, to track outcomes over time.A diagnostic interview study, using a clinical diagnostic measure to ascertain the true prevalence of mental disorders.A qualitative interview study, using semistructured interviews to explore experiences of using (or reasons for not using) staff support programmes.

The study will be carried out in 18 NHS Trusts in locations across England.

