#### Diagnostic interview study

Participants will be up to 350 HCWs who have completed the baseline NHS CHECK survey.

Up to 250 participants will be purposively sampled according to their responses to the General Health Questionnaire (GHQ) in the short survey module;^13^ half will meet caseness and half will not meet caseness. These participants will be administered the Clinical Interview Schedule-Revised (CIS-R).^14^ The number of CIS-R interviews (n=250) has been chosen balancing precision and cost. Based on a simulation study, we anticipate that 250 interviews will allow estimation of CIS-R prevalence of common mental disorders to within ±6%.

Up to 100 HCWs will be sampled according to their responses to the 6-item PTSD Checklist civilian version (PCL-6)^15^ in the long survey module; half will meet caseness and half will not meet caseness. These participants will be administered the Clinician-administered PTSD Scale (CAPS-5).^16^ This sample size was calculated as the necessary number to achieve a valid estimation of PTSD prevalence.

Sampling for the CIS-R and CAPS-5 groups will be stratified to ensure representation from each of the 18 participating sites in the NHS CHECK Study, as well as to ensure ethnic, sex and age breakdown that resembles respondents of the baseline survey.

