#### Diagnostic interview study

This study will validate the screening questionnaires used for general distress and PTSDs using diagnostic interviews with the CIS-R and the CAPS-5, respectively. Participants for the validation studies will be randomly selected from those with non-missing screening scores in a 50% ratio of caseness or otherwise. Sample sizes were obtained by simulation studies (n=250 and 100, respectively, for the CIS-R and CAPS-5 diagnostic interviews). Sensitivity, specificity, and positive and negative predictive values will be calculated. If possible, prevalence values for the population at risk will be calculated using population weightings (which will be derived from sex, age and ethnicity variables in an attempt to ensure representativeness in the sample population). Sensitivity analyses will be undertaken to account for missingness if necessary.

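### True prevalence by interview is a primary objective and both interview samples were sized for it, yet the analysis plan makes prevalence conditional and names weights that ignore the 50/50 screen split

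*Protocol article*

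**What the plan says.** **Objectives.** In the protocol article, Aims, objectives and hypotheses, the primary objective includes "psychiatric diagnostic interviews to determine the true prevalence of disorders". The list that follows has "Establish the true prevalence of mental disorders via diagnostic interviews" ahead of the secondary objectives. Design and setting defines the component as "A diagnostic interview study, using a clinical diagnostic measure to ascertain the true prevalence of mental disorders".

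**Sample size.** Under Study population and sample, Diagnostic interview study, the CIS-R sample is justified by precision of prevalence: "we anticipate that 250 interviews will allow estimation of CIS-R prevalence of common mental disorders to within ±6" per cent. For the 100 CAPS-5 interviews it says: "This sample size was calculated as the necessary number to achieve a valid estimation of PTSD prevalence". Each sample is half screen-positive and half screen-negative.

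**Analysis.** Under Analysis plan, Diagnostic interview study, the stated purpose becomes "This study will validate the screening questionnaires used for general distress and PTSDs using diagnostic interviews". Sensitivity, specificity, PPV and NPV are promised without condition. Prevalence is not: "If possible, prevalence values for the population at risk will be calculated using population weightings". Those weightings are described as coming from sex, age and ethnicity. The screen result is not mentioned as a weighting variable.

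**The concern.** The objectives and sample-size text treat prevalence as what the interviews are for. The analysis section treats it as optional, and treats as certain a validation exercise that appears in no listed objective. A team that reported the accuracy measures and stopped would have complied with the analysis plan while leaving a primary objective unanswered.

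The weighting clause adds a second problem. Interviewees are chosen half and half by screen result, so the raw proportion diagnosed is not a prevalence unless exactly half of respondents screen positive. If prevalence is calculated with only the weights named, the primary estimate can be materially biased.

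**Working it through.** **1. The plan's own figure.** The simulation inputs behind ±6% for CIS-R are not given, so it cannot be reproduced exactly. It is plausible. A simple random sample of 250 gives 1.96·√(0.5·0.5/250) = 6.2 points at a prevalence of 50%, and 1.96·√(0.3·0.7/250) = 5.7 points at 30%. The figure is not disputed.

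**2. Is prevalence computable from this design?** Let π be the screen-positive rate, PPV the disorder rate in screen-positives, f the disorder rate in screen-negatives, and n₁, n₀ the interviews in each half.

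- Prevalence: p = π·PPV + (1−π)·f
- 95% half-width: 1.96·√[π²·PPV(1−PPV)/n₁ + (1−π)²·f(1−f)/n₀]

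The documents give n₁ = n₀ = 125 (CIS-R) and 50 (CAPS-5), but not π, PPV or f. Those are assumptions.

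| | π | PPV | f | p | half-width (points) |
|---|---|---|---|---|---|
| CIS-R | 0.50 | 0.40 | 0.08 | 24.0% | 1.96·√(0.000480+0.000147) = 4.9 |
| CAPS-5 | 0.30 | 0.30 | 0.02 | 10.4% | 1.96·√(0.000378+0.000192) = 4.7 |

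Over wider ranges the half-width is:

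- CIS-R: 3.6 to 6.0 points (π 0.30–0.60, PPV 0.30–0.70, f 0.05–0.20)
- CAPS-5: 3.0 to 6.4 points, on prevalences of 3.8% to 17.9% (π 0.20–0.35, PPV 0.15–0.40, f 0.01–0.06)

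So the estimate can be made, and for CIS-R at about the stated precision.

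**3. What the screen weight does.** With a 50/50 split the uncorrected proportion is (PPV+f)/2. Its error is (PPV+f)/2 − p = (0.5−π)·(PPV−f).

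- CAPS-5, on the assumptions above: (0.30+0.02)/2 = 16% against 10.4%. The error is 0.20·0.28 = 5.6 points.
- CIS-R: no error at π = 0.50. With PPV and f as above, it is +0.20·0.32 = +6.4 points at π = 0.30 and −0.10·0.32 = −3.2 points at π = 0.60.

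The interview sample is already to be stratified to resemble baseline respondents by ethnicity, sex and age, so demographic weights cannot be expected to remove this error.

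**4. Subordinate point: PTSD sensitivity.** Screen-weighted sensitivity is π·PPV/[π·PPV + (1−π)·k/50], where k is the number of cases among the 50 screen-negatives. With π = PPV = 0.30:

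- k = 0, 1, 2, 3 gives 100%, 86.5%, 76%, 68%.
- At k = 1, exact limits for the rate in screen-negatives (0.05% to 10.6%) put sensitivity between 55% and 99.6%, holding π and PPV fixed.
- The chance of k = 0 is (1−f)⁵⁰: 61% at f = 1%, 36% at 2%, 13% at 4%.

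**The case against.** **The committed outputs already fix prevalence.** PPV and NPV are promised, and the cohort analysis promises weighted prevalence of the survey outcomes. Since p = π·PPV + (1−π)·(1−NPV), the ingredients would exist. This stands against any claim that the primary objective has no route to an estimate. It does not remove the contradiction: the plan never says the ingredients will be combined, and the one sentence that mentions doing so is conditional.

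**The condition may qualify only projection to the wider population.** That reading is possible. But under equal sampling by screen result an unweighted figure is not a prevalence, so if the weighting is optional, so is the estimate.

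**The SAP may settle it.** It may name the sampling weight. The article, however, does not merely leave detail out. It states a condition that conflicts with its own objectives, and it says what the weights are derived from.

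**The eligibility list complicates matters.** The inclusion criteria for the interviews include meeting GHQ or PCL-6 caseness, which read literally leaves no screen-negatives. Both the sampling and analysis sections specify half and half, so the calculations follow those. The criterion needs reconciling separately.

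**Stronger readings that a reader might infer, and that the documents do not support:**

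- *The plan leads with sensitivity.* It lists four measures together and ranks none.
- *The samples were not sized for accuracy.* The simulations are not shown. The text states a prevalence purpose but does not exclude accuracy targets.
- *Prevalence is what the design estimates best.* On the PTSD assumptions above, NPV (±3.9 points) and specificity (±3.3, by simulation) are tighter than prevalence (±4.7).
- *A reported PTSD sensitivity of 100% is a likely chance result.* The probability is 36% at an assumed 2% rate and varies widely with that rate.

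**Conclusion.** The concern holds as an internal contradiction. Prevalence by interview is a primary objective and the stated basis of both sample sizes, but the analysis section makes it conditional and guarantees only accuracy measures. This part rests on the text alone.

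The weighting gap is of practical size for PTSD: 5.6 points on a prevalence of 10.4%, under assumed rates of 30% screen-positive, PPV 30% and 2% of screen-negatives affected. The direction depends on the screen-positive rate. Prevalence is overstated when fewer than half screen positive and understated when more than half do.

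The imprecision of PTSD sensitivity is secondary. It rests on assumed rates and concerns the 50 PTSD screen-negatives, not the 125 for CIS-R. The same 50 also limit PTSD prevalence, where ±4.7 points on 10.4% is about ±45% in relative terms.

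**What to change.** In the Analysis plan, Diagnostic interview study:

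1. Delete the words *If possible*. Commit to the prevalence of common mental disorder (CIS-R) and of PTSD (CAPS-5), each with a 95% CI, as a primary analysis of the interview study.
2. State that these estimates are weighted back to the screen-positive and screen-negative proportions among survey respondents (short survey for GHQ, long survey for PCL-6), as well as by sex, age and ethnicity. Apply the same screen weight to sensitivity and specificity.
3. Keep the accuracy measures as companion outputs, and acknowledge that PTSD sensitivity will be imprecise with 50 screen-negatives.

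This needs no new interviews or data. The cost is a little analysis wording and a more modest claim for validation of the PTSD screen.

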
## Methods

### Design and setting

This study consists of three main components:

A longitudinal cohort study, consisting of surveys administered at baseline, 6 months and 12 months, to track outcomes over time.A diagnostic interview study, using a clinical diagnostic measure to ascertain the true prevalence of mental disorders.A qualitative interview study, using semistructured interviews to explore experiences of using (or reasons for not using) staff support programmes.

The study will be carried out in 18 NHS Trusts in locations across England.

### Study population and sample

#### Longitudinal cohort study

Participants across the study will be any NHS-affiliated staff including clinical staff, students and all support staff working within participating NHS Trusts: Avon and Wiltshire Mental Health NHS Foundation Trust (n=4334); Cambridge University Hospitals NHS Foundation Trust (n=10 243); Cambridgeshire and Peterborough NHS Foundation Trust (n=4235); Cornwall Partnership NHS Foundation Trust (n=3977); Devon Partnership NHS Foundation Trust (n=3280); East Suffolk and North Essex NHS Foundation Trust (n=10 219); Gloucestershire Hospitals NHS Foundation Trust (n=8437); Guys and St Thomas' NHS Foundation Trust (n=19 760); King’s College Hospital and Princess Royal University Hospital (PRUH) (n=12 959); Lancashire and South Cumbria NHS Foundation Trust (n=6984); Norfolk and Norwich University Hospitals (n=10 502); Nottinghamshire Healthcare NHS Foundation Trust (n=8860); Royal Papworth Hospital (n=2110); Sheffield Health and Social Care (n=2610); South London and Maudsley NHS Foundation Trust (n=5151); Tees Esk and Wear Valleys NHS Foundation Trust (n=7315); University Hospitals of Derby and Burton (n=13 231); University Hospitals of Leicester NHS Foundation Trust (n=16 946); and/or any of the Nightingale Hospitals (London, Exeter, Leeds/Harrogate, Cardiff and Manchester), dependent on whether these sites are active at the time of data collection. Study sites were selected to cover multiple areas of England. All staff in each study site will be invited to participate.

#### Diagnostic interview study

Participants will be up to 350 HCWs who have completed the baseline NHS CHECK survey.

Up to 250 participants will be purposively sampled according to their responses to the General Health Questionnaire (GHQ) in the short survey module;^13^ half will meet caseness and half will not meet caseness. These participants will be administered the Clinical Interview Schedule-Revised (CIS-R).^14^ The number of CIS-R interviews (n=250) has been chosen balancing precision and cost. Based on a simulation study, we anticipate that 250 interviews will allow estimation of CIS-R prevalence of common mental disorders to within ±6%.

Up to 100 HCWs will be sampled according to their responses to the 6-item PTSD Checklist civilian version (PCL-6)^15^ in the long survey module; half will meet caseness and half will not meet caseness. These participants will be administered the Clinician-administered PTSD Scale (CAPS-5).^16^ This sample size was calculated as the necessary number to achieve a valid estimation of PTSD prevalence.

Sampling for the CIS-R and CAPS-5 groups will be stratified to ensure representation from each of the 18 participating sites in the NHS CHECK Study, as well as to ensure ethnic, sex and age breakdown that resembles respondents of the baseline survey.

